### Measures

All primary outcomes came directly from the US Health and Human Services (HHS) Common HIV Indicators for the HRSA/SPNS project (FOA HRSA-15-029). Utilization of these collection procedures provided data that could be compared with other clinical services and programs serving high-risk populations and populations that are underrepresented in HIV care. As the ETAC cross-site evaluation procedures and measures are described in detail elsewhere [48], only the local evaluation measures are described below.

#### Local Evaluation for Text Me, Girl! Only

The Local Evaluation was a behavioral assessment that included questions in the following domains: gender identity and presentation including hormone use, sexually transmitted infections, sexual behaviors, and HIV self-efficacy. The assessment measures that were used as part of the local (not cross-site) evaluation component of *Text Me, Girl!* are described below.

##### HIV Health Assessment

Originally developed by the principal investigator (PI) [name], for an intensive prevention case management intervention, this instrument records demographics (eg, sexual identity, age, and racial/ethnic identities), educational attainment, housing status, access to insurance, HIV treatment status (including position in the HIV care continuum), HIV medication status (including medication type and dose) and self-reported ART adherence, and barriers to receiving HIV care [49]. Only the domains specific to the outcome measurements of this study that did not duplicate the ETAC cross-site evaluation were used.

##### The Los Angeles Transgender Health Survey

This instrument was developed by [name] and colleagues in 1997 in consultation with members of the LAC transgender women communities and appropriately updated in the interim years. The instrument comprises 7 modules: screening, sociodemographic characteristics, health care access and medical history, sexual behaviors (at all stages of gender transition and gender confirmation surgery), drug and alcohol use, legal and psychosocial issues, and HIV prevention [50]. Only the domains specific to the outcome measurements of this study and those that did not duplicate the HIV health assessment or the ETAC cross-site evaluation were used.

##### HIV Treatment Adherence Self-Efficacy Scale

The HIV treatment adherence self-efficacy scale (HIV-ASES) comprises 12 items assessing participants’ self-efficacy to adhere to their ART medication regimen (0=cannot do it at all to 10=completely certain can do). Cronbach alpha for the measure is robust (routinely >.90). The HIV-ASES is lightly adapted to the target populations’ lower average literacy level and refers specifically to participants’ level of confidence that they can maintain adherence. The scale assessed how confident participants were to integrate treatment into daily routines, stick to a treatment plan even if it was disruptive or they felt unwell, continue treatment plan even if the level of T cells drops significantly, and get something positive out of participation in treatment even if the medication did not seem to improve their health [51].

### Statistical Analyses

Table 2 provides all evaluation outcomes and their chosen measurement models. Power calculations are based on assumptions of alpha=.05 (2-tailed tests), a sample size of 130 HIV-positive young transgender women, and a power standard of 0.80. It was calculated that logistic regression analyses of primary outcomes would be able to find a minimum detectable odds ratio of 2.98 for linkage/uptake of ART and achievement of an undetectable viral load (the primary outcomes of interest).

**Table 2 table2:** Study outcomes and measurement models.

Primary outcome	Measurement model
Linkage to HIV primary care (self-report and EMR^a^/EHR^b^ abstraction)	0= Participant did not attend HIV medical visit within 3 months of enrollment; 1= Participant attended within the first 3 months
Prescribed ART^c^ medication (self-report and EMR/EHR abstraction)	0=Participant is not prescribed HIV medication; 1=Participant is prescribed HIV medication
Retention in HIV primary care (self-report and EMR/EHR abstraction)	0=Participant did not attend a second HIV care appointment after the initial 3 months; 1=Participant attended an additional HIV primary care visit after the initial 3 months
ART adherence (self-report)	Ordinal scale (Likert)
Viral load monitoring (self-report and EMR/EHR abstraction)	Binary (0=>200 copies/mL, 1=<200 copies/mL)

^a^EMR: electronic medical report.

^b^EHR: electronic health report.

^c^ART: antiretroviral therapy.

All regression analyses assess assumptions of normality and model fit. In addition to the primary outcomes listed in Table 2, participants were assessed for changes in their HIV-related self-efficacy from baseline to follow-up evaluations. The HIV-ASES scale was used to assess HIV self-efficacy, producing continuous values suitable for ordinary least squares (OLS) regression. In addition, if during implementation, a sufficient number of participants opted in to receive one or more of the postintervention retention/engagement text messages available through final distal follow-up evaluation, additional analyses were carried out to estimate the observed effect(s) of receiving these postintervention text messages.

All calculations of detectable effects for primary outcomes were based on expected cultural/demographic subgroup analyses premised on known social determinants of risk (eg, racial/ethnic identity, language and health insurance) and are displayed in Table 2. Secondary analyses related to HIV self-efficacy were analyzed using OLS regression and should produce detectable effects at *f*^2^=0.067. Given these values, detectable effects of all analyses should, if benchmarked, fall in the *small to moderate* to *moderate* ranges. Given an expected follow-up rate of at least 85% (111/130) at each time point, associations between primary outcomes and optional postintervention retention/engagement messages should produce minimum detectable effects exhibiting a 3% (repeated measures survival analysis testing time-based dichotomous outcomes, eg, linkage) to 18% (OLS regression for secondary analyses, eg, HIV-related self-efficacy scores) increase in detectable effect size (ie, outcomes will be more difficult to detect), resultant from participant attrition.

Primary outcome analyses comprised bivariate contrasts of outcomes over time (ie, HIV care continuum outcomes at baseline and each follow-up, with differences tested via *t* test and chi-square analyses) and multivariate analyses of these same outcomes regressed on random study arm assignment, self-reported exposure to theory-based text messages, and time. Observations were nested within participants, and sociodemographic controls were tested for inclusion during sensitivity testing of the models. Secondary outcomes included sexual risk behaviors, substance use, self-efficacy, and changes in gender identity over time.

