#### Random Assignment

After completing the baseline assessment, participants were assigned to a condition through an urn randomization procedure. The urn randomization procedure provided balance across age (18-24 and 25-34 years), race/ethnicity (Latino/Hispanic and all other race/ethnicities), and HIV care continuum status (linked, nonlinked to HIV care). Participants were randomized into 1 of the 2 conditions: Group A—immediate text message intervention delivery (n=61) or Group B—delayed text message intervention delivery (n=69) whereby participants were delivered the text-messaging intervention after a 90-day delay period. Both groups received the same 90-day text-messaging intervention. The randomized 2-group repeated measures design assessed participants at 3, 6, 12, and 18 months post randomization.

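### OLS is named for HIV-ASES change over four follow-ups without the within-participant nesting stated for the primary models; a baseline-adjusted repeated-measures analysis would be safer and more precise

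*Protocol article*

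**What the plan says.** Under Statistical Analyses, the article says that "participants were assessed for changes in their HIV-related self-efficacy from baseline to follow-up evaluations" and that the HIV-ASES does so by "producing continuous values suitable for ordinary least squares (OLS) regression". It then repeats the method with a detectable effect: "Secondary analyses related to HIV self-efficacy were analyzed using OLS regression and should produce detectable effects at" f² = 0.067. OLS is named a third time in the attrition sentence, which gives an 18% increase in the detectable effect for self-efficacy when follow-up is 85% (111 of 130).

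Under Random Assignment, the design is described thus: "The randomized 2-group repeated measures design assessed participants at 3, 6, 12, and 18 months post randomization". Group A (n=61) receives the texts at once. Group B (n=69) receives the same 90-day programme after a 90-day delay.

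The statement that observations are clustered by participant comes directly after the description of the multivariate primary-outcome models. Self-efficacy appears in the next sentence, in a list of secondary outcomes with no model attached.

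**The concern.** Each woman can contribute up to four follow-up scores and a baseline score, and these will be correlated. Plain OLS treats every record as independent. The article recognises clustering for its primary models but names only OLS for HIV-ASES, so a reader cannot tell how the repeated scores are handled.

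There are two natural ways to carry out the stated method:

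- **Pool the visits.** The standard errors are then wrong, in a direction that depends on the contrast.
- **Fit each visit separately on the change score.** The test is valid but uses less of the available information than a baseline-adjusted model.

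The choice of visit also matters. Group B receives the intervention after its delay, so month 3 is the only scheduled follow-up that contrasts texts with no texts. The plural follow-up evaluations name no contrast.

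**Working it through.** **Inputs from the article.** N = 130; two-sided alpha 0.05; power 0.80; four follow-ups; 111 of 130 retained; stated f² = 0.067; stated attrition effect 18%.

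**Assumption.** The article gives no within-woman correlation r for HIV-ASES. I use r = 0.3, 0.5 and 0.7, with equal variances σ² and equal correlation between all visits.

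**Step 1: what the stated detectable effect implies.** I used noncentral F power with one tested predictor, noncentrality f² × N and error df = N − 2, solved for 80% power.

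| Records | Detectable f² |
|---|---|
| 130 (one per woman) | 0.0613 |
| 111 (one per woman, after attrition) | 0.0720 |
| 520 (130 × 4 pooled) | 0.0152 |
| 444 (111 × 4 pooled) | 0.0178 |

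The stated 0.067 is not reproduced exactly; it fits N of about 119 to 120, and at N = 130 it would give power 0.834. It clearly lies on the one-record-per-woman scale, about four times the pooled values. The attrition increase is 0.0720 / 0.0613 = 1.174, or 17.4%, close to the stated 18%. Both figures point to one record per woman in the power calculation.

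**Step 2: if change scores from four visits were pooled in plain OLS to test arm.** Let D_j = Y_j − Y_0.

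- Var(D_j) = 2σ²(1 − r).
- Cov(D_j, D_k) = σ²(r − r − r + 1) = σ²(1 − r).
- The correlation between two change scores is therefore (1 − r) / [2(1 − r)] = 0.5, whatever r is, because all share one baseline.
- Design effect = 1 + 3 × 0.5 = 2.5.
- Reported SE / true SE = 1/√2.5 = 0.63, an understatement of 37%.
- True error of a nominal 5% test = 2 × [1 − Φ(1.96/√2.5)] = 0.215.

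**Step 3: if raw scores were pooled to estimate change over time.** For the within-woman contrast of baseline with follow-up, the true variance is (1 − r) times what independence assumes. The OLS standard error is too large by 1/√(1 − r): 1.20, 1.41 and 1.83 at r = 0.3, 0.5 and 0.7. Here the intervals are too wide.

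**Step 4: if each visit is fitted separately.** Residual variance is 2σ²(1 − r) for an unadjusted change score and σ²(1 − r²) when baseline is a covariate.

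| r | Change score | Baseline-adjusted | Variance ratio 2/(1 + r) | SE ratio |
|---|---|---|---|---|
| 0.3 | 1.40 | 0.91 | 1.54 | 1.24 |
| 0.5 | 1.00 | 0.75 | 1.33 | 1.15 |
| 0.7 | 0.60 | 0.51 | 1.18 | 1.08 |

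Variances are in units of σ²; the SE ratio is the square root of the variance ratio.

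**The case against.** Two stronger readings are tempting, and the article supports neither.

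- **That the analysis leaves out the baseline score.** A reader might infer this from the mention of change and OLS. But analysis of covariance is itself OLS, and the article neither includes nor excludes baseline as a covariate. The variance ratios in Step 4 apply only if a plain change score is used.
- **That visits are pooled as if independent, so that error is inflated over a wide range.** Nothing says the visits are pooled, and Step 1 points the other way. Using raw-score design effects of 1 + 3r (1.9, 2.5, 3.1), one can compute errors of 15.5%, 21.5% and 26.6%, but those belong to an arm effect averaged over pooled raw scores. For change scores, the quantity the article describes, the figure is a single 21.5% under the stated assumptions. For change over time in raw scores the error runs in the opposite direction.

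Three further points for the plan are fair. OLS with participant-clustered errors would deal with the correlation. The nesting statement shares a paragraph with the list of secondary outcomes, so its scope is ambiguous rather than plainly restricted. And a condensed article commonly leaves covariates and the type of standard error to a full analysis plan, so silence on those details is not in itself a fault. In addition, with complete data the month-3 contrast from a mixed model is close to OLS of the month-3 score on arm and baseline.

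What remains is that the method is not left open. OLS is named three times for an outcome in a design the article itself calls repeated measures, and it is not tied to the nesting described for the primary models. The power figure describes the calculation and does not by itself fix the analysis.

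**Conclusion.** The point holds as a modest improvement to a secondary outcome; it does not show that the analysis is invalid. Plain OLS on HIV-ASES change is either wrong in its standard errors (pooled) or less precise than it could be (per-visit change scores).

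The pooled case gives about 21.5% true error for a nominal 5% test of arm on change scores; this rests on equal variances and correlations and on pooling, which the article does not state. The per-visit case, which fits the stated f² better, is valid with residual variance about 1.5, 1.3 or 1.2 times that of a baseline-adjusted analysis; this rests on the assumed correlations and on baseline not being a covariate. The primary outcomes are not affected.

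**What to change.** Replace the OLS statement for HIV-ASES with one of these:

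- a linear mixed model with visit, arm by visit and baseline HIV-ASES as a covariate, and either a participant random intercept or an unstructured covariance across visits; or
- OLS with baseline HIV-ASES as a covariate and standard errors clustered by participant.

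In either case, name the arm difference at month 3 as the randomised contrast, because it precedes Group B's texts, and describe later visits separately. The mixed model also uses the scores of women who miss a visit, which is useful when up to 15% may be absent at each time point. A random intercept alone assumes equal correlation between visits from 3 to 18 months; the unstructured option avoids that.

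The cost is one or two sentences and a little more modelling work. No new data are needed, the baseline score is part of the planned assessment of change, and both analyses are standard in Stata, which the article already names.

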#### Postintervention Opt-In/Opt-Out Retention and Engagement Text Messages

Immediately following the 90-day text-messaging intervention, participants were offered an opportunity to opt in to receive additional weekly text messages at a reduced schedule through their final distal follow-up evaluation. Participants in both study conditions could opt to receive the postintervention messages. Postintervention retention/engagement messages comprised 2 topic areas: (1) linkage/retention support (ie, participant received a message about linking/remaining in HIV care) and (2) ART adherence reminders (ie, participant received a message about the importance of medication adherence); a participant could opt in to any one or both of the topic areas. Each of the 2 topic areas were transmitted once a week for a maximum of 2 weekly messages. Postintervention retention/engagement messages were derived directly from the text messages already available through the Health Resources and Services Administration (HRSA)–funded UCARE4LIFE library. At each follow-up visit, participants were asked if they wanted to opt in/out to receive these additional retention/engagement text messages and were informed that they could stop the additional messages at any time by texting back *stop* to the system.

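### The planned effect estimate for the optional weekly messages rests on self-selected receipt in both arms, and linkage, an outcome named for it, is settled before those messages can start

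*Protocol article*

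**What the plan says.** The section on postintervention messages says that, once the 90-day course ended, "participants were offered an opportunity to opt in to receive additional weekly text messages at a reduced schedule through their final distal follow-up evaluation". The offer was not tied to the allocation: "Participants in both study conditions could opt to receive the postintervention messages". It was also repeated: "At each follow-up visit, participants were asked if they wanted to opt in/out to receive these additional retention/engagement text messages". Between visits, women were told that "they could stop the additional messages at any time by texting back" a keyword. The two message topics are linkage/retention in care and ART adherence, which are also outcome domains in Table 2.

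Statistical Analyses makes the analysis conditional ("if during implementation, a sufficient number of participants opted in to receive one or more" of these messages) and then states its aim: "additional analyses were carried out to estimate the observed effect(s) of receiving these postintervention text messages". Further on, the same section describes the analysis as "associations between primary outcomes and optional postintervention retention/engagement messages". It gives linkage as an example of the time-based binary outcomes and puts the loss of detectable effect from attrition at 3% to 18%. The only covariate adjustment it describes is sociodemographic controls, tried in sensitivity models.

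**The concern.** Women decided for themselves whether to receive the optional messages, and could change that decision. The same offer was open to both arms, so random assignment does not separate recipients from non-recipients. Whatever leads a woman to accept, continue or stop may also predict whether she attends HIV care, takes ART or is virally suppressed. Sociodemographic controls do not capture engagement or care status at the time of the choice.

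A second problem is order in time. An outcome that is already fixed when the messages become available cannot be caused by them. If such outcomes enter the analysis, the optional messages may be credited with, or blamed for, events that came first.

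At stake is the reading of the add-on. An association described as an effect of receipt could support, or count against, adding weekly messages to the course when they made no difference.

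**Working it through.** **1. The article's own figure.** The upper attrition figure for this analysis is 18%, for follow-up of 85% (111/130). The plain ratio is 1/0.85 = 1.176, an increase of 17.6%, which rounds to 18%. A noncentral F calculation (one tested predictor, two-sided alpha 0.05, power 0.80) gives a minimum detectable f² of 0.0613 at N=130 and 0.0720 at N=111, an increase of 17.4%. So 18% is essentially reproduced. It reflects lost sample size only and says nothing about bias from self-selection. The 3% figure was not reproduced, and nothing below depends on it.

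**2. Timing, from the article's own definitions.**

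| | Group A | Group B |
|---|---|---|
| 90-day course (Random Assignment) | day 0 to about 90 | about day 90 to 180 |
| Earliest optional message | about month 3 | 90 + 90 = 180 days, about month 6 |
| Linkage window (Table 2) | closes at month 3 | closes at month 3 |
| Retention can first be met (Table 2) | after month 3 | after month 3 |

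- Linkage: in Group B the window closes about 3 months before any optional message can be sent. In Group A it closes at about the time the first could be sent. If receipt is coded as ever opted in, linkage precedes exposure. If receipt is updated over time, there is essentially no exposed time inside the window. Neither coding can yield an effect on linkage as defined.
- Retention: a Group B woman can meet this outcome between months 3 and 6, before any optional message. In either arm, a woman who first opts in at a later visit may already have met it.

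**3. What self-selection alone can produce.** The article gives no opt-in rate and no outcome rates by engagement, so every rate here is an assumption. Half the women are taken as highly engaged and the true effect of the messages is zero. Let a and b be the opt-in rates, and y and z the outcome rates, in the high and low engagement halves:

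- outcome rate in opt-ins: p1 = (a·y + b·z)/(a + b)
- outcome rate in the rest: p0 = ((1−a)·y + (1−b)·z)/((1−a) + (1−b))
- OR = [p1/(1−p1)] / [p0/(1−p0)]

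Example with opt-in 70/30% and outcome 80/40%: p1 = (0.56 + 0.12)/1.0 = 0.68; p0 = (0.24 + 0.28)/1.0 = 0.52; OR = 2.125/1.083 = 1.96.

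| Opt-in, high/low | Outcome, high/low | p1 | p0 | OR | Chance of p<0.05 |
|---|---|---|---|---|---|
| 60/40% | 60/40% | 0.52 | 0.48 | 1.17 | 6% |
| 60/40% | 70/50% | 0.62 | 0.58 | 1.18 | not computed |
| 70/40% | 80/50% | 0.691 | 0.600 | 1.49 | not computed |
| 70/30% | 70/30% | 0.58 | 0.42 | 1.91 | 39% |
| 80/20% | 70/30% | 0.62 | 0.38 | 2.66 | 72% |
| 80/20% | 80/20% | 0.68 | 0.32 | 4.52 | 98% |
| 40/60% (need-driven) | 70/30% | 0.46 | 0.54 | 0.73 | not computed |

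The last column is for N=111 with half opting in (n=55.5 per group), two-sided alpha 0.05: power = Φ{[(p1−p0) − 1.96·√(2·0.5·0.5/n)] / √[(p1(1−p1)+p0(1−p0))/n]}. For 0.58 v 0.42: (0.16 − 0.186)/0.0937 = −0.28, which gives 39%.

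**The case against.** The strongest case against the point is that this is a conditional, supplementary analysis in a condensed article. No comparator, exposure coding or adjustment set is given, and a fuller plan may hold them, so their absence proves nothing. One sentence qualifies the effects as observed, and a later one already speaks of associations.

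Much of this stands, and it rules out several stronger readings:

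- A reader might infer that the article states a comparison of choosers with non-choosers. It does not; that contrast is a natural inference. The point does not need it, because with the same offer open to both arms, a before-and-after contrast would be self-selected too.
- A reader might infer that the estimate will simply measure engagement and falsely favour the messages. The documents do not support that certainty. Women who are struggling may opt in more, which reverses the bias. Stopping is the active step between visits, so a disengaged woman may keep receiving messages. The first offer is not tied to attending a visit. Paid study visits are also not the same behaviour as HIV care visits.
- A reader might infer that later results will be presented as durability of the 90-day course alone. Nothing in the article claims that, and the opt-in for both arms is openly described.

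The objection does not remove the conflict between offering the messages after the course, fixing linkage within 3 months, and naming linkage as an outcome for this analysis. That lies in the stated text and is not missing detail.

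**Conclusion.** The point holds in a limited form. The analysis of the optional messages cannot identify an effect of receiving them. It is open to confounding by engagement or need and to timing bias. The linkage conflict follows from the article's definitions without any assumed rate, and so does the possibility that Group B women meet the retention outcome before any optional message.

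The size of confounding cannot be derived from the article. With half the women engaged and no true effect, the assumed rates give odds ratios from 1.17 to 4.52 when engaged women opt in more, and 0.73 when they opt in less. These show what is possible and are not a forecast.

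The point is worth correcting, but its reach is small: it concerns one conditional analysis and leaves the randomised month-3 comparison untouched.

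**What to change.** - In Statistical Analyses, replace the effect wording with a non-randomised association, in line with the term used later in the same section.
- Drop linkage as an outcome for this analysis.
- Use opt-in status at the previous visit to predict the outcome at the next visit, adjusting for arm and for outcome status at the time of the choice.
- Count only events dated after opt-in, which also removes retention visits made before a woman's first optional message.
- Report opt-in by arm and visit beside all results after month 3, so that readers can see who was still receiving messages.

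Cost: the claim for the optional messages becomes weaker, and each woman contributes one fewer usable interval. No new visits or participants are needed, and the article places the primary outcome analyses after follow-up ends. The article does not say whether opt-in dates, stop requests and care-visit dates are held in usable form, so that should be checked first. If they are not, report opt-in descriptively only.

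### The analysis of optional postintervention messages names linkage as an example outcome, but linkage as coded in Table 2 closes at month 3, essentially before any such message can be sent

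*Protocol article*

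**What the plan says.** Four statements in the protocol article bear on this.

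- **Outcome.** Table 2 codes linkage as "0= Participant did not attend HIV medical visit within 3 months of enrollment; 1= Participant attended within the first 3 months". The Statistical Analyses section introduces the table with "Table 2 provides all evaluation outcomes and their chosen measurement models", and the article gives no other definition of linkage.
- **Start of exposure.** The section on postintervention opt-in/opt-out messages states: "Immediately following the 90-day text-messaging intervention, participants were offered an opportunity to opt in to receive additional weekly text messages". Opting in is voluntary, open to both groups, and offered again at each follow-up visit. Each of two topics is sent once a week.
- **Group B timing.** Under Random Assignment, Group B is the arm in which "participants were delivered the text-messaging intervention after a 90-day delay period".
- **Analysis.** If enough women opted in, "additional analyses were carried out to estimate the observed effect(s) of receiving these postintervention text messages". The attrition paragraph of the same section then refers to associations between the primary outcomes and these messages, and says that "optional postintervention retention/engagement messages should produce minimum detectable effects exhibiting a 3% (repeated measures survival analysis testing time-based dichotomous outcomes, eg, linkage". The upper end of its range is 18%, for ordinary least squares regression of secondary outcomes.

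**The concern.** An exposure can affect only what happens after it starts. The text pairs an exposure that starts after the 90-day course with an outcome that closes at about the time the course ends in Group A, and about three months before it ends in Group B. Relating the two would compare women who had linked with women who had not, by whether they later chose to receive messages. Women already in care may opt in more readily, or general engagement may drive both. One of the two message topics concerns linking to and staying in care, so a positive result would invite a causal reading. Reported as an effect of receiving the messages, it would be a false claim for that component.

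**Working it through.** **The plan's own figures.** Attrition takes the sample from 130 to 111.

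- The 18% reproduces approximately. The simple ratio is 130/111 = 1.171, or 17.1%. Solving the noncentral F distribution for the minimum detectable f² at two-sided alpha 0.05 and power 0.80 gives, for one tested predictor, 0.0613 at N=130 and 0.0720 at N=111, a rise of 17.4%. For five tested predictors the rise is 18.1%.
- The 3% does not follow from the stated inputs. On a log-odds or log-hazard scale, √(130/111) = 1.082, or 8.2%. The repeated-measures inputs are not given, so the 3% cannot be called wrong. The point here does not depend on it.

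**Timeline, linkage.** Day 0 is randomization. It is taken as the enrollment date because "After completing the baseline assessment, participants were assigned to a condition through an urn randomization procedure", and the Enrollment section places that assessment in the enrollment session. Group A is assumed to start its course on day 0; a later start would only reduce the overlap.

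| Event | Group A | Group B |
|---|---|---|
| 90-day course begins | day 0 | day 90 |
| Earliest offer of opt-in messages | day 90 | day 90 + 90 = 180 |
| Linkage window closes (3 calendar months) | day 89 to 92 | day 89 to 92 |
| Window left after earliest offer | at most 92 − 90 = 2 days | none; closed 88 to 91 days earlier |

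The range of 89 to 92 days comes from counting three calendar months from every date between the first enrollment (December 16, 2016) and the close of enrollment (May 31, 2018). The Results section agrees with the Group B timing: May 31, 2018 plus 180 days is November 27, 2018, and delivery ended on November 30, 2018.

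**Timeline, retention.** Table 2 counts a further visit after the initial three months. In Group B the first 88 to 91 days of that window (180 − 92 and 180 − 89) come before any opt-in message is possible, so a qualifying visit in that stretch cannot be due to the messages. In Group A the window opens at about the time of the first offer. Because the offer is repeated at later visits, a woman in either group who opts in late may also have a qualifying visit before her own exposure.

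**The case against.** The strongest reply has four parts.

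- **Linkage is only an illustration.** It appears in parentheses, in a sentence about attrition, and the analysis depends on enough women opting in. This is true and limits the weight of the point. Even so, linkage is the only primary outcome named for this analysis, and the sentence covers the primary outcomes generally.
- **Repeated-measures survival analysis of time-based outcomes suggests time to first visit, not a single indicator closed at month 3.** On that reading, women still unlinked at the offer could link later because of the messages. This is a fair reading, and a reader should not infer that no linkage effect is possible under any definition. But the article defines no such outcome, and Table 2 is said to hold them all. The two places need reconciling either way.
- **The details belong in an analysis plan that is not shown.** Modelling detail does, and its absence is not the point. The conflict is between an outcome, an exposure and an analysis that the article itself states.
- **The article speaks of associations and describes opt-in openly.** It does, but the same section also sets out to estimate the effect of receiving the messages.

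Three further inferences are not supported. An association need not be reverse causation: self-selection or chance would also produce one. The 3% covers a class of time-based dichotomous outcomes, so it need not be deleted because linkage is a poor example. And Table 2 gives retention no end date, so the share of its window lost in Group B cannot be stated.

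**Conclusion.** The point holds for linkage as coded in Table 2. Apart from at most about 2 days of rounding in Group A, the outcome is settled before exposure to the postintervention messages can begin, so an association between them cannot be an effect of the messages. Retention is affected in part, mainly through visits between months 3 and 6 in Group B.

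This rests on two assumptions: that enrollment and randomization fall at about the same time, and that Table 2 is the operative definition of linkage.

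The reach is limited to a conditional, nonrandomized supplementary analysis. A reader might infer that the trial's linkage result is compromised. It is not: the randomized Group A versus Group B comparison does not use the postintervention messages as its exposure. ART prescription, adherence and viral load measured after opt-in do not share the timing fault, though exposure remains self-selected for them.

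**What to change.** - Exclude linkage as coded in Table 2 from the postintervention-message analysis. If time to first visit among women still unlinked at the offer was meant, define that outcome and reconcile Table 2 with the attrition paragraph.
- Tie the 3% figure to an outcome that can occur after exposure.
- For retention and the other outcomes, count only events or measurements dated after each woman's own opt-in.
- Report the result as a nonrandomized association, not as an effect of receiving the messages.

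The cost is wording and date handling, assuming that opt-in and visit dates were recorded; the article does not say that they were, and linkage and retention come partly from self-report. The Results section places the primary outcome analyses after August 31, 2019, so the text could be corrected before they begin.
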